**Questions about the PET-MRI**							
It was comfortable	0	1	2	3	4	5	n/a
I felt scared	0	1	2	3	4	5	n/a
It took too long	0	1	2	3	4	5	n/a
The noise bothered me	0	1	2	3	4	5	n/a
I was reluctant to undergo the scan	0	1	2	3	4	5	n/a
It went better than expected	0	1	2	3	4	5	n/a
The PET-MRI contrast agents caused discomfort	0	1	2	3	4	5	n/a
**Questions about the PET-CT**							
It was comfortable	0	1	2	3	4	5	n/a
I felt scared	0	1	2	3	4	5	n/a
It took too long	0	1	2	3	4	5	n/a
The noise bothered me	0	1	2	3	4	5	n/a
I was reluctant to undergo the scan	0	1	2	3	4	5	n/a
It went better than expected	0	1	2	3	4	5	n/a
The PET-CT contrast agents caused discomfort	0	1	2	3	4	5	n/a
**Comparing PET-CT to PET-MRI**							
The PET-MRI was less of a burden than the PET-CT	0	1	2	3	4	5	n/a
It didn’t matter that the PET-MRI took longer than the PET-CT	0	1	2	3	4	5	n/a
If the results are equally good, I prefer the PET-MRI over the PET-CT	0	1	2	3	4	5	n/a
If the results of the PET-MRI are *better* than the PET/CT, I would prefer the PET-MRI over the PET-CT	0	1	2	3	4	5	n/a

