**Comments**							

0: Don’t know. 1: Strongly disagree. 2: Disagree. 3: Neither agree nor disagree. 4: Agree. 5: Strongly agree. n/a: not applicable.

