### Imaging

A summary of imaging steps is provided in Table 
2. PET imaging will be conducted according to EANM guidelines
[17]. 18 F-FDG will be administered while the patient is supine on the PET-MRI table using MR compatible devices. The MRI will be performed during the period in which FDG distributes throughout the body, and PET will commence approximately 60 minutes after FDG injection. The PET of the PET-CT will follow 20 minutes (±5) after completion of the PET-MRI, followed by a whole body low-dose CT for attenuation and image-fusion and a diagnostic 4-phase liver CT. This scanning sequence has been chosen to minimize the burden for the patient, to optimize reliability of the dedicated liver MRI sequences and to minimize the time between both PET scans.

**Table 2 T2:** Imaging protocol and timeline of PET-MRI and PET-CT (T = approximate time in minutes)

T = 0	Injection FDG	
T = 5	Start MRI	Axial T2-weighted imaging
		T1 in- and opposed phase GRE
		Diffusion-weighted imaging
		Fat-suppressed T1-weighted eThrive (contrast enhanced)
		- pre-contrast
		- arterial phase (bolus tracking)
		- portovenous phase (70 sec delay)
		- late venous phase (200 sec delay)
		Attenuation sequence (skullbase – midthigh)
		Whole body T1-weighted mDixon (skullbase – midthigh)
T = 60		PET skullbase – midthigh
T = 75	**End PET-MRI**	**Transfer to PET-CT**
T = 95	Start PET-CT	PET skullbase – midthigh
		low dose CT
		4-phase CT liver
		- pre-contrast
		- arterial phase (bolus tracking)
		- portovenous phase (70 sec delay)
		- late venous phase (240 sec delay)
T = 145	End PET-CT	

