The period between FDG injection and acquisition of the PET-CT in this study is 30 minutes longer than the standard protocol, which might increase our ability to detect intrahepatic malignancies. Background activity in the normal liver parenchyma due to high glucose metabolism and abundant expression of Glut-1 and Hexokinase II can often impede detection of liver lesions. Following a rationale that FDG accumulates over time in malignant cells as compared to healthy or inflamed hepatocytes, several authors have proposed that PET-CT imaging may improve lesion detectability over time through an improvement in the tumor-to-background ratio
[24,25]. It is known that FDG uptake by a tumor may not plateau before 90–120 minutes and peak levels may persist for up to 4 hours after injection
[26]. Using target-liver ratios, we will investigate whether the 30 minutes delay between both PET-scans contribute to an improved differentiation of post-ablation inflammation and residual tumor
[15]. The study has not been designed to provide semi-quantitative values for FDG uptake as predictors of therapeutic response, generally expressed as the standard uptake volume (SUV). However, the SUV can vary considerably and the time lapse between FDG injection and acquisition is a major contributor to this variation
[27].

Follow-up is only worthwhile when patients comply to a physician’s recommendations, and compliance with medical advice has been a challenge since first described by Hippocrates
[28]. Numerous factors determine whether a person’s behaviour coincides with medical advice, such as the duration of therapy, the complexity of the regimen and psychosocial factors
[29]. Adherence to follow-up can also be affected by a patients’ negative experience of examinations such as discomfort and pain
[30,31]. These patient preferences may contribute to final decision making on follow-up imaging, especially when modalities are known to be equally effective. We formulated the hypothesis that PET-MRI provides a less favourable experience when compared to PET-CT, as the MRI examination may elicit anxiety due to the need to remain immobile and alone while enclosed in the MRI tunnel for a prolonged period of time, in addition to the noise associated with the examination
[32].

In this study, we solely focus on the ability of PET-MRI to identify intrahepatic recurrences, since most recurrences after local treatment of the liver reoccur in the liver

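### All four head-to-head preference items in Table 1 are worded so that agreeing favours PET-MRI, which exposes the direct preference result to agreement bias

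*Protocol article*

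**What the plan says.** Patient preference is a secondary outcome (Primary and secondary objectives). It is assessed once, after the fourth PET-MRI, with a purpose-built questionnaire printed in full as Table 1. The table has three blocks.

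- Seven items on PET-MRI and the same seven on PET-CT. In each block two are worded positively (comfort; better than expected) and five negatively (fear, length, noise, reluctance, contrast discomfort).
- Four comparison items:
  1. "The PET-MRI was less of a burden than the PET-CT"
  2. "It didn’t matter that the PET-MRI took longer than the PET-CT"
  3. "If the results are equally good, I prefer the PET-MRI over the PET-CT"
  4. A statement that, should PET-MRI give better results, "I would prefer the PET-MRI over the PET-CT"

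The answers are "1: Strongly disagree. 2: Disagree. 3: Neither agree nor disagree. 4: Agree. 5: Strongly agree", with 0 for don't know and a not-applicable option. There is also a comments field.

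The Discussion gives the expected direction: "We formulated the hypothesis that PET-MRI provides a less favourable experience when compared to PET-CT". It adds that patients' preferences may play a part in choosing follow-up imaging, especially between equally effective modalities.

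**The concern.** Some respondents tend to agree with a statement whatever it says. A questionnaire usually guards against this by wording some items in each direction, or by offering a two-sided choice. The comparison block does neither, so any such tendency moves every item towards PET-MRI.

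Two items have a further weakness. Item 4 asks whether the patient would prefer the scan that gives better results, so most people will agree whatever their experience was. Item 2 tells the patient that PET-MRI took longer and asks only whether that mattered.

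At stake is how the direct preference answers can be read. A majority for PET-MRI could partly reflect the wording. Because the hypothesis points the other way, the wording would tend to hide the expected finding, not create it. Once answers have been collected, no analysis can separate wording from preference within this block.

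**Working it through.** The article gives no numerical figure for the questionnaire, so there is none to reproduce. The check is a count of item direction, a short argument about what cancels, an illustration and a look at the time premise.

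**Direction of the comparison items (Table 1)**

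| Item | Agreement means | Statement put from the PET-CT side? |
|---|---|---|
| 1 Burden | PET-MRI less of a burden | No |
| 2 Duration | Longer PET-MRI accepted | No |
| 3 Equal results | PET-MRI preferred | No |
| 4 Better PET-MRI results | PET-MRI preferred | No |

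Four of four favour PET-MRI and none favours PET-CT.

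**What cancels and what does not.** Let a respondent's tendency to agree add *c* to every answer (a simplification on a bounded scale).

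- Paired blocks: each item has the same wording for both scans, so the within-patient difference is (m + c) − (t + c) = m − t, where *m* and *t* are the PET-MRI and PET-CT answers. The tendency drops out.
- Comparison block: each answer is one number, x + c, with nothing to subtract. Over four items in one direction the total shift is (4 − 0) × c = 4c. With two items each way it would be (2 − 2) × c = 0.

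**Illustration of size.** Assumptions: one item; 20 patients (Sample size calculation), all giving a non-neutral answer; an exact two-sided sign test at 0.05 (the article gives 0.05 without stating sidedness and names no test for this item); and a shift *a* in the probability of agreeing, for which the documents give no value.

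Critical value: 2 × P(X ≥ 15 | 20, 0.5) = 2 × 0.0207 = 0.041, so 15 of 20 are needed. Indifferent patients agree with probability 0.5 + a. If 75% truly favour PET-CT, they disagree with probability 0.75 − a.

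| Assumed shift a | Indifferent patients: P(significant for PET-MRI) | 75% favour PET-CT: P(this is shown) |
|---|---|---|
| 0 | 2.1% | 61.7% |
| 5 points | 5.5% | 41.6% |
| 10 points | 12.6% | 24.5% |
| 15 points | 24.5% | 12.6% |
| 20 points | 41.6% | 5.5% |

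A two-sided item has nothing to agree with. If that removes the tendency altogether, the row a = 0 applies.

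**The time premise (Table 2).** PET-MRI ends at T = 75: 75 minutes from injection, or 75 − 5 = 70 minutes from the start of MRI. PET-CT runs from T = 95 to T = 145, which is 50 minutes. PET-MRI is thus longer by 20 to 25 minutes, and item 2 is factually correct for these patients. Its weakness is that it supplies the premise; the paired items on whether each scan was too long ask about duration without one.

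**The case against.** The best defence is that the comparison block is only part of the questionnaire. The hypothesis concerns experience, with anxiety and immobility, noise and prolonged duration in the MRI tunnel given as reasons. The paired blocks ask about fear, noise and length for each scan in identical words. A reader might infer that the hypothesis is poorly tested, or can be supported only by disagreement. The documents do not support that. The paired blocks stand, although they contain no question on preference between the scans and so do not repair the comparison items.

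The scale is also symmetric and has a midpoint. On the equal-results item an indifferent patient can choose 3 and a patient who prefers PET-CT can choose 1 or 2. It would go too far to say that a PET-CT preference cannot be expressed. Some ambiguity remains: a patient who found the scans equally burdensome can truthfully disagree with item 1.

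A reader might also conclude that the result is biased by a known amount, such as 2 to 4 of 20 patients (10–20% of 20). That rate would be an assumption, and the count would hold only if each of those patients would otherwise not have agreed. On item 4 few such patients are likely to exist.

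Finally, a reader might infer that the single FDG injection creates the time difference, since "PET will commence approximately 60 minutes after FDG injection" and the wait is spent in the MRI. The shared injection does spare PET-CT an uptake wait of its own. The difference in scanner time, however, comes mostly from the MRI protocol, whose dedicated liver imaging alone takes about 45 minutes (MRI section). A comparison with a separate PET-CT visit would need times that the article does not state. The 50 minutes cannot simply be carried over either, because PET-CT bed time is adjusted to the interval since injection.

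**Conclusion.** The point holds as a wording risk in the four direct comparison items. All run towards PET-MRI, one nearly answers itself with no counterpart, and one presumes a time difference. This rests on the printed text alone. The direction of any bias is clear, towards PET-MRI and against the stated hypothesis, but its size cannot be derived from the document. The tabulated figures rest on an assumed shift and on 20 non-neutral answers; they show only that at this sample size a modest wording effect could matter.

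The documents support no more than exposure to bias in the direct preference result. The paired items still give a fair comparison of experience. This is a minor improvement to a secondary outcome, and the accuracy aims are unaffected.

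**What to change.** - Replace items 1 and 3 with two-sided questions: which scan was the greater burden, and which would be chosen if results were equally good. Each offers PET-CT / no difference / PET-MRI.
- Delete item 4, or add the same question with PET-CT giving the better results.
- Remove the presumed time difference from item 2, or drop the item, since the paired items on length already cover duration. Do not give patients hypothetical times for separate visits.
- Keep the two seven-item blocks unchanged, as the within-patient comparison of experience.

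The cost is rewording four lines of a purpose-built form that each patient completes only after the fourth PET-MRI. Answers already collected on the present wording should be reported separately and not pooled with the new items.

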**Comments**							

0: Don’t know. 1: Strongly disagree. 2: Disagree. 3: Neither agree nor disagree. 4: Agree. 5: Strongly agree. n/a: not applicable.

### Patients

Written informed consent will be obtained from all participants. Patients scheduled to undergo either RFA/MWA of CRLM, solely or in combination with resection, or RFA/MWA for LTP after previous thermal ablation of CRLM, will be recruited at a referral university hospital (VU University Medical Center, Amsterdam, the Netherlands) and a large community teaching hospital (Gelderse Vallei, Ede, the Netherlands). Assessment prior to ablation consists of a full-body 18 F-FDG PET-CT and 4-phase liver CT or MRI of the liver. Increased FDG uptake of the CRLM on the pre-operative PET scan is a requirement. All patients will be discussed by a multidisciplinary liver board prior to treatment and suitability for RFA or MWA will be at their discretion. Treatment will depend, amongst others things, on the number, location and size of lesions. An open approach using intra-operative ultrasound is preferred as an initial treatment, and a CT-guided percutaneous approach will be used for treatment of recurrences. Technical success, or was the tumor ablated according to protocol, was required before inclusion
[16]. Our protocol defines a complete ablation as the entire size of the tumor plus a 1 cm tumor free margin as seen on IOUS or CT. This area was calculated during the planning phase of the procedure.

Exclusion criteria are chemotherapy within 6 weeks prior to the first scan, allergies to contrast media and general contraindications for MRI. Patients with an eGFR <60 will be admitted for additional hydration before and after the scans. If chemotherapy is initiated or if the ablated lesion is resected during the first year of follow-up, participation in the study will be aborted.

### Study procedure

The standard follow-up protocol during the first year after RFA/MWA of CRLM in the VU University Medical Center consists of three-monthly whole-body FDG PET-CT and 4-phase liver CT, in combination with measurement of serum carcinoembryonic antigen (only when elevated pre-operatively). For the purposes of this study, liver FDG PET-MRI will be added to the routine procedure, using a 3.0 Tesla Ingenuity TF Philips scanner (Philips Medical Systems, Cleveland, OH). This hybrid PET-MRI system is characterized by a sequential acquisition mode and has separate scanners with a turntable patient handling system facilitating patient motion between the MRI and the PET gantries that are located at a 3 meter distance from each other.At the end of one year follow-up, patients will be asked to complete a questionnaire evaluating their experience with the PET-MRI compared to the PET-CT. The study procedure is illustrated in Figure 
1.

**Figure 1 F1:**
[figure not shown]
Flow diagram of study procedure.

### Imaging

A summary of imaging steps is provided in Table 
2. PET imaging will be conducted according to EANM guidelines
[17]. 18 F-FDG will be administered while the patient is supine on the PET-MRI table using MR compatible devices. The MRI will be performed during the period in which FDG distributes throughout the body, and PET will commence approximately 60 minutes after FDG injection. The PET of the PET-CT will follow 20 minutes (±5) after completion of the PET-MRI, followed by a whole body low-dose CT for attenuation and image-fusion and a diagnostic 4-phase liver CT. This scanning sequence has been chosen to minimize the burden for the patient, to optimize reliability of the dedicated liver MRI sequences and to minimize the time between both PET scans.

**Table 2 T2:** Imaging protocol and timeline of PET-MRI and PET-CT (T = approximate time in minutes)

T = 0	Injection FDG	
T = 5	Start MRI	Axial T2-weighted imaging
		T1 in- and opposed phase GRE
		Diffusion-weighted imaging
		Fat-suppressed T1-weighted eThrive (contrast enhanced)
		- pre-contrast
		- arterial phase (bolus tracking)
		- portovenous phase (70 sec delay)
		- late venous phase (200 sec delay)
		Attenuation sequence (skullbase – midthigh)
		Whole body T1-weighted mDixon (skullbase – midthigh)
T = 60		PET skullbase – midthigh
T = 75	**End PET-MRI**	**Transfer to PET-CT**
T = 95	Start PET-CT	PET skullbase – midthigh
		low dose CT
		4-phase CT liver
		- pre-contrast
		- arterial phase (bolus tracking)
		- portovenous phase (70 sec delay)
		- late venous phase (240 sec delay)
T = 145	End PET-CT	

#### MRI

A 16-channel Sense Torso XL coil is connected and a low-resolution non-diagnostic MR attenuation sequence (atMRI) (skull base to mid-thigh) is run, followed by a whole body T1-weighted mDixon sequence, scanned in the axial plane to allow for anatomical matching of FDG images
[18]. These images are routinely reconstructed in the coronal plane. Dedicated axial liver imaging is performed: axial T2-weighted TSE (TR/TE 850/80 msec); T1 in- and opposed phase GRE (TR/TE 180/2.3/1.15 msec) and diffusion-weighted imaging (TR/TE 2407/53 msec) using b-values (0, 50 and 800 sec/mm^2^). This is followed by a fat-suppressed T1-weighted GRE using IV Gadolinium-chelate at 0.1 mmol/kg (Dotarem, 0.5 mmol/ml; Guerbet, Gorichem, The Netherlands) in 4 separate phases: pre-contrast, arterial phase (determined by a bolus tracking method to ensure optimal arterial enhancement, which includes full enhancement of the hepatic artery and only partial enhancement of the portal vein
[19]), as well as 70 and 200 msec post-injection. Total imaging time for the dedicated liver protocol is approximately 45 minutes.

#### 18F-FDG PET (PET-MRI)

After MRI, the PET-MRI table is turned and the patient is placed in the PET gantry. The PET features an 18 cm axial field of view, 9 cm overlap between bed positions and a 5.5 mm reconstructed isotropic spatial resolution. The scan trajectory covers the skull base to mid-thigh, taking 2 min/bed position. Reconstructed images have an image matrix size of 144X144, voxel size of 4X4 mm and slice thickness of 5 mm. Data are reconstructed by means of a Blob-OS-TF algorithm. Fusion images are created with the PET sequence and atMRI, mDixon axial and coronal whole body and axial T2 liver.

#### 18F-FDG PET (PET-CT)

The Philips Gemini TF PET-CT system (Philips Medical Systems, Cleveland, Ohio, USA) is comparable to the PET unit of the PET-MRI. Scanning is started with a whole body PET (skull base to mid-thigh), with data being reconstructed by means of a raw action ordered subset expectation maximization algorithm using default reconstruction parameters. Time of flight (TF) information is used during reconstruction. Reconstructed images have an image matrix size of 144X144, a voxel size of 4X4 mm and a slice thickness of 5 mm. The acquisition time per bed position is adjusted for the time interval between the start of PET-CT and FDG injection and will usually be 2–3 min/bed position.

#### Low-dose CT

This is followed by a low-dose CT for attenuation and image fusion and is collected using a beam current of 30–50 mAs at 100 keV. The low-dose CT is reconstructed using an image matrix of 512X512, resulting in voxel sizes of 1.17X1.17 mm and a slice thickness of 5 mm.

#### 4-phase liver CT

A diagnostic 4-phase CT of the liver using 100 ml Xenetix300 (Guerbet, Villepinte, France) is subsequently performed, using a beam current of 175-220mAs per slice. First, a precontrast scan is run, followed by the arterial phase using a bolus-tracking method and a 80 keV scan to ensure optimal arterial enhancement
[20]. During the venous phase, 70 sec post-injection, the entire abdomen is scanned, followed by a scan of the liver in the late venous phase (240 sec post-injection), both at 120 keV. The images are reconstructed using a matrix of 512X512 and a slice thickness of 3–5 mm. All images are sent to a digital picture archive and communication system (PACS; Sectra AB, Linköping, Sweden).

### Image analysis

Only PET-CT and 4-phase liver CT images will be analysed and used in the context of routine patient care during clinical follow-up. The PET-MRI images will not be part of the diagnostic and follow-up process.

For imaging analysis, blinded data sets of all scans will be viewed both separately and independently by two designated, experienced radiologists and two nuclear medicine physicians. The reviewers will be blinded to the results of the other imaging modalities and to final patient outcome. A time-interval of at least four weeks will be introduced between the first and second review. Progressive disease will be scored on a per-patient and per-lesion basis, and results of all imaging modalities will be compared. The criteria for progression on different modalities are defined in Table 
3. Each lesion on each modality will be scored on a separate form and results will be scored from 1–5 (Table 
4) and size and location of the lesions will be reported. A LTP is defined as a lesion located in or within 1 cm of the ablation zone; a new intrahepatic lesion is defined as a lesion located more than 1 cm distant from the ablation zone
[6]. On MRI, a suspicious lesions has to meet the definition of LTP in at least two different sequences before it is considered positive for progression.

**Table 3 T3:** Test positivity criteria for progressive disease on different imaging modalities; ≤1 cm of the ablation zone (LTP) / >1 cm of the ablation zone (new intrahepatic recurrence)

ceCT		Newly detectable hypodense lesion
MRI	T1	New focal hypo-intense lesion
	T2	New focal hyper-intense lesion
	Contrast enhanced	Irregular peripheral enhancement pattern of a circumscribed lesion
	Diffusion weighed	Lesion with high signal intensity on b800
FDG PET		Lesion with clearly increased focal uptake as compared to liver background

**Table 4 T4:** Study form for reviewers’ results (per lesion base)

**Study number:**		**Reviewer number:**
**Score**	**Definition**	**Explanation**
1	Normal	Confident that no tumor recurrence is present in the ablation zone/confident that no new intrahepatic lesions are present
2	Probably benign	The appearance of the ablated lesion is compatible with post-ablational inflammation or rim-like characteristics/the new lesions diagnosed do not appear malignant
3	Equivocal	There is doubt whether the enhanced FDG, CT- and/or MRI features indicate tumor progression or inflammation/there is doubt whether the new lesions diagnosed are benign or malignant
4	Probably malignant	Confident of local progression in the ablation zone/confident of new intrahepatic metastases
		Size or estimated size:
		Location:
		Intensity FDG vs normal liver; slight/moderate/intense
5	Impaired quality	Quality of the images precludes adequate diagnosis
Comments:		

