**Methods/Design:**

Twenty patients undergoing treatment with radiofrequency or microwave ablation for (recurrent) CRLM will be included in this prospective trial. During the first year of follow-up, patients will be scanned at the VU University Medical Center at 3-monthly intervals using a 4-phase liver CT, FDG PET-CT and FDG PET-MRI. Patients treated with chemotherapy <6 weeks prior to scanning or with a contra-indication for MRI will be excluded. MRI will be performed using both whole body imaging (mDixon) and dedicated liver sequences, including diffusion-weighted imaging, T1 in-phase and opposed-phase, T2 and dynamic contrast-enhanced imaging. The results of all modalities will be scored by 4 individual reviewers and inter-observer agreement will be determined. The reference standard will be histology or clinical follow-up. A questionnaire regarding patients’ experience with both modalities will also be completed at the end of the follow-up year.

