### Primary and secondary objectives

We will assess the effectiveness of FDG PET-MRI in the follow-up of thermal ablation (RFA/MWA) of CRLM. Our primary aim will be to assess the accuracy of FDG PET-MRI in the diagnosis of local progression in the first year after RFA/MWA of CRLM. Therefore, all FDG PET-MRI images will be compared to FDG PET-CT and 4-phase liver CT images, which are the current standard of care. Results of different imaging sets will be compared on a per-patient and a per-lesion base. These results will then be compared to a reference standard: either histological outcome (if available) or clinical follow-up.

Secondary outcomes will include the accuracy of diagnosis of new intrahepatic disease after RFA/MWA. Since only a single 18 F-FDG per combined PET-MRI and PET-CT visit will be applied, we will have the opportunity to investigate whether dual-time point PET can increase the specificity of the 18 F-FDG signal and increase diagnostic accuracy
[15]. The reproducibly and robustness of inter-observer variation will also be determined. Clinical relevance will be studied by recruiting a panel consisting of a radiologist, interventional radiologist, nuclear medicine physician, oncologist, oncological surgeon and a radiation oncologist to retrospectively review PET-MRI images and agree on the preferred treatment. Choice of treatment based on PET-MRI will then be compared to the treatment that was actually received based on PET-CT and 4-phase liver CT. Finally, patients’ preferences will be assessed at one year follow-up using a specifically designed questionnaire that compares both modalities (Table 
1).

**Table 1 T1:** Questionnaire comparing PET-CT and PET-MRI (completed following fourth PET-MRI)

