### Sample size calculation

Sample size estimates are based on the incidence of local site recurrences and new intrahepatic metastases. Previous studies have shown that 25-40% of the patients treated with RFA/MWA develop LTP, of which >95% occur within the first year
[4]. In addition, 30-40% of the patients will develop new intrahepatic metastases
[2,21]. At least 5 LTP and 5 new intrahepatic lesions are necessary for a meaningful comparison between PET-CT and PET-MRI in this observational study. Using the binominal distribution (with *p* = 0.35 and n = 20), the chance of finding 5 LTP and the chance of finding 5 new intrahepatic lesions in our population are both 88%. This suggests that the study has a satisfactory chance of success with a sample size of 20 patients. Patients excluded during the study period will be replaced by new participants, so that 20 patients will have completed one year follow-up at study completion.

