### Statistical analysis

We will determine the accuracy of PET-MRI for diagnosing recurrent disease compared to each imaging method (MRI, CT and PET-CT) and compared to pathology or clinical follow-up. Continuous variables will be summarized with standard descriptive statistics including means, standard deviations, medians and ranges when indicated. Categorical variables will be summarized with frequencies. McNemar’s test is used to determine agreement between PET-MRI and other modalities. The inter-observer variability will be quantified with Cohen’s Kappa and proportions of specific agreement. P-values less than 0.05 will be considered statistically significant. Statistical analysis will be performed using SPSS version 20.0 (SPSS Inc, Chicago).

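### The per-lesion comparison is planned with an ordinary McNemar test, which ignores that lesions are clustered in 20 patients; the effect is modest unless visits or readers are also pooled

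*Protocol article*

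**What the plan says.** The unit of comparison is given twice. Primary and secondary objectives: "Results of different imaging sets will be compared on a per-patient and a per-lesion base". Image analysis: "Progressive disease will be scored on a per-patient and per-lesion basis, and results of all imaging modalities will be compared". The latter section also gives every lesion its own form for each modality.

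Statistical analysis names one test for comparing the modalities: "McNemar’s test is used to determine agreement between PET-MRI and other modalities". For agreement between readers it names kappa together with specific agreement, and it sets the significance threshold at 0.05. It plans no confidence intervals and no test of kappa.

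The data come from few patients, each seen repeatedly. Patients are replaced "so that 20 patients will have completed one year follow-up at study completion" (Sample size calculation). Scans are three-monthly for a year, and Table 1 refers to a fourth PET-MRI. Abstract, Methods/Design: "The results of all modalities will be scored by 4 individual reviewers". The Patients section foresees more than one lesion per patient, since treatment depends partly on lesion number. No passage allows for several results from the same patient, or says how visits and readers are reduced to the pairs that are tested.

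**The concern.** McNemar's test takes the discordant pairs as independent. Two lesions in one liver share the scan session, the FDG uptake, the liver background and the reader, so a modality that misses one may well miss the other. With positive correlation the ordinary test understates the variance of the difference, and its p-value is too small.

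The numbers are small enough for this to matter. The sample size section asks for only 5 local progressions and 5 new lesions, so one or two patients with several lesions could decide the per-lesion result and set it against the per-patient one.

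Pooling visits would add a second problem. PET-MRI does not guide care (Image analysis), whereas suspicion on CT or PET-CT leads to evaluation for re-treatment (Recurrent disease and repeated treatment). A lesion seen only on PET-MRI could therefore recur as a discordant pair at later visits more often than one seen on PET-CT. That would favour PET-MRI, which the Background expects to be superior for new intrahepatic lesions.

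**Working it through.** **1. The plan's own figure.** With n = 20 and p = 0.35, the binomial probability of at least 5 events is 0.8818, which agrees with the stated 88%. The calculation treats each patient as one independent trial. The sample size is thus per patient, while the comparison is also per lesion.

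**2. Inputs.** From the article: 20 patients, about 4 visits, 4 readers, level 0.05 (two-sided assumed). Assumed, because the article gives none of them: m pairs per patient (2 or 3 lesions at one visit; 8 = 2 lesions × 4 visits), discordance q of 20 or 30%, and within-patient correlation ρ of 0.3 or 0.5 in the direction of discordance. There is no true difference between modalities.

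**3. Formula.** If direction clusters but occurrence does not, the variance of the difference is inflated by D = 1 + (m − 1)qρ. The large-sample size of a nominal 5% test is 2[1 − Φ(1.96/√D)].
- m = 3, q = 0.3, ρ = 0.3: D = 1 + 2 × 0.09 = 1.18; size about 7.1%. An interval computed under independence has 1/√1.18 = 92% of its proper width.
- m = 8, q = 0.3, ρ = 0.3: D = 1 + 7 × 0.09 = 1.63; size about 12.5%; width 78%.

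**4. Simulation at 20 patients** (20,000 runs per setting, direction of discordance beta-binomial). False-positive rates for ρ = 0.3 / 0.5:

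| Pairs per patient | Discordance | Exact McNemar | Chi-square, uncorrected |
|---|---|---|---|
| 2 | 20% | 2.1 / 2.3% | 4.8 / 5.1% |
| 2 | 30% | 3.2 / 3.7% | 5.3 / 6.1% |
| 3 | 20% | 3.3 / 4.2% | 5.6 / 6.8% |
| 3 | 30% | 4.7 / 5.7% | 7.5 / 8.9% |
| 8 | 20% | 7.4 / 9.9% | 10.4 / 13.2% |
| 8 | 30% | 10.1 / 14.7% | 12.4 / 17.3% |

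For reference, at ρ = 0 and 30% discordance the exact test has size 2.4% (m = 2), 3.0% (m = 3) and 3.7% (m = 8), because it is conservative in small samples. Clustering uses up that margin before it passes 5%. A patient-clustered McNemar statistic, (Σdᵢ)²/Σdᵢ² with dᵢ the net discordance in patient i, stays at about 4 to 5% in all these settings.

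**5. Stronger clustering.** If the occurrence of discordance also clusters (20% discordance, ρ = 0.3 / 0.5), 3 pairs give 4.4 / 7.5% (exact) and 7.2 / 11.7% (chi-square). Eight pairs give 12.3 / 22.4% and 16.2 / 27.0%.

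**6. Readers pooled too.** With m = 2 × 4 × 4 = 32 and 30% discordance, the rates are 30.2 / 39.7% (exact) and 31.9 / 41.4% (chi-square).

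**7. What pooling visits can do in one patient.** Two lesions seen only on PET-MRI at three visits give 6 discordant pairs against 0, and exact p = 2 × 0.5⁶ = 0.031. With each lesion counted once there are 2 against 0, and p = 2 × 0.5² = 0.5.

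**The case against.** The best defence is that the large effects belong to an analysis that the article does not describe. It does not say that visits or readers enter as separate pairs, and a condensed article may leave that reduction to the full protocol or SAP. This stands: the figures for 8 and 32 pairs show what pooling would do, not what is planned. With lesion clustering alone, the exact test stays near or below 5% in most settings.

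Two further points stand. No confidence intervals and no kappa test are planned, so nothing stated there is too narrow, and kappa as a point estimate is not invalidated. Positive correlation is plausible but not documented.

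The visit asymmetry also has limits. A reader might infer that a PET-CT-positive lesion is always treated and stops contributing. The section on recurrent disease does not support this: patients continue after repeat ablation of a local progression, those with locally treated new lesions remain while the initial ablation area is unaffected, and doubtful findings are rescanned.

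What the defence does not remove is that the article itself names the per-lesion unit, the test and the threshold. The problem is that stated combination, not a missing detail. The one-result-per-patient comparison is unaffected.

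**Conclusion.** The point holds in a limited form. An ordinary McNemar test does not suit per-lesion pairs nested in 20 patients, and its p-values are likely to be too small if within-patient correlation is positive. At 2 to 3 lesions per patient and one visit the inflation is modest: about 2 to 6% with the exact test and 5 to 9% with chi-square, somewhat more if the occurrence of discordance also clusters. At 8 pooled pairs per patient it is roughly 7 to 17%, and higher under stronger clustering.

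A reader might infer that the plan as written carries a false-positive rate of 20% or more. The article does not support that, since such rates need pooling that it neither states nor excludes, together with strong clustering or pooled readers. All sizes rest on assumed lesion counts, discordance and correlation. The change is worth making because the remedy is cheap and the number of events is small.

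**What to change.** - Keep the per-patient comparison, with one result per patient and modality, as the main one.
- For per-lesion comparisons, replace the ordinary test with a patient-clustered McNemar test (Obuchowski or Durkalski), or a patient-level bootstrap of the paired difference in sensitivity and specificity.
- Let each lesion contribute one result per modality under a rule fixed in advance. The rule must also cover lesions that are never positive, for example status over the whole follow-up year. A rule tied to the first positive visit would give those lesions no visit and leave specificity undefined.
- Do not treat readers as independent pairs. Report per reader, or average over readers within the patient-level bootstrap.
- Base any precision reported for kappa on resampling patients.

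The cost is a few sentences of analysis text, a short script outside the SPSS menus and slightly wider per-lesion intervals. Scans, readings and sample size do not change.
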